## Abstract

**Background:**

Distance running is a popular recreational exercise. It is a beneficial activity for health and well being. However, running may also cause injuries, especially of the lower extremities. In literature there is no agreement what intrinsic and extrinsic factors cause running related injuries (RRIs). In theory, most RRIs are elicited by training errors, this too much, too soon. In a preconditioning program runners can adapt more gradually to the high mechanical loads of running and will be less susceptible to RRIs. In this study the effectiveness of a 4-week preconditioning program on the incidence of RRIs in novice runners prior to a training program will be studied.

**Methods/Design:**

The GRONORUN 2 (Groningen Novice Running) study is a two arm randomized controlled trial studying the effect of a 4-week preconditioning (PRECON) program in a group of novice runners. All participants wanted to train for the recreational Groningen 4-Mile running event. The PRECON group started a 4-week preconditioning program with walking and hopping exercises 4 weeks before the start of the training program. The control (CON) and PRECON group started a frequently used 9-week training program in preparation for the Groningen 4-Mile running event.

During the follow up period participants registered their running exposure, other sporting activities and running related injuries in an Internet based running log. The primary outcome measure was the number of RRIs. RRI was defined as a musculoskeletal ailment or complaint of the lower extremities or back causing a restriction on running for at least three training sessions.

**Discussion:**

The GRONORUN 2 study will add important information to the existing running science. The concept of preconditioning is easy to implement in existing training programs and will hopefully prevent RRIs especially in novice runners.

**Trial registration:**

The Netherlands National Trial Register NTR1906. The NTR is part of the WHO Primary Registries.

## Background

Running is a popular activity and can be practised everywhere. The health benefits are substantial but runners get injured regularly. The incidence of running related injuries (RRIs) is high. Various studies in different populations reported rates of RRIs ranging from 19-79% [1-9]. RRIs are often located in the lower extremities with knee and lower leg mostly affected [3,6,7,10-12]. There is no agreement on the cause of RRIs. In the current literature, possible intrinsic and extrinsic risk factors are identified, but there is still no exact cause for an RRI. Van Mechelen [13] and van Gent et al [9] proposed risk factors that have been significantly related to RRI; excessive weekly running distance, previous injury, lack of running experience and competitive running.

Clinical studies showed that over 60% of RRIs could be attributed to training errors [14]. Hreljac [14] stated that all overuse running injuries are the result of training errors. From this point of view a RRI is a disturbance between the external load applied to the body and the injury threshold of a biological structure of the body. In this dose-response relationship there are four components applicable to the novice runner [14]. The first component is the current status of the musculoskeletal system of the novice runner. The second component is the type of applied stress (i.e. running). Thirdly, the frequency, intensity and duration of the applied stress (i.e. running) and finally, the adaptation and recovery times between running sessions are major determinants of this dose relationship.

Under normal circumstances the musculoskeletal system adapts to the level of stress placed upon it [14-16]. When an optimal level of stress is applied to the musculoskeletal system, along with an adequate recovery time, the musculoskeletal system will increase in strength. On the other hand, when the applied stress is too high or the recovery time is too short the tissue of the musculoskeletal system will be weakened and the likelihood of sustaining a subsequent overuse injury is high [14,16,17]. Mechanical load (i.e. running) applied to the human body can cause a physiological or pathological adaptation to this mechanical loading, resulting in respectively a training effect or overuse injury [17].

The musculoskeletal system of the novice runner is normally not adapted to the repetitive and relatively high impact forces of running because novice runners are frequently physically inactive before they start to run [10,18]. In most regular running programs for novice runners the biomechanical load is high from the start of the program in terms of frequency, intensity and duration.

The first GRONORUN study [7,19] showed that previous sports participation without axial loading was an important predictor for RRIs in novice runners. From this knowledge a strategy can be chosen to strengthen the lower extremities to achieve a positive physiological adaptation of the musculoskeletal system before starting a training program for novice runners. The applied external load of this so called preconditioning program will stress the lower extremities and as a result the lower extremities will positively adapt to the applied stress. In this way there is a stepwise transition of biomechanical load which makes it easier for the musculoskeletal system of the lower extremities to withstand the demands of running. Other studies in athletes and military populations [20-23,23] showed a positive effect of a preconditioning program on the incidence of sports and overuse injuries in different populations.

In a preconditioning program for running, the program needs to load the musculoskeletal system in a sport-specific way. Therefore, in this randomized controlled trial a preconditioning program with walking and hopping prior to the training program for novice runners will be studied. We hypothesize that the novice runner can adapt more gradually to the external impact forces of running with a preconditioning program prior to the training program and will be less susceptible to RRIs.

## Methods/design

The GROningen NOvice RUNing 2 (GRONORUN 2) study is a randomized controlled trial with a 13-week follow-up. Participants were randomized into two groups: an active control (CON) group and an intervention (PRECON) group. The PRECON group will receive a 4-week preconditioning program prior to the start of the training program. Recruitment of participants for the GRONORUN 2 study took place in the period April - June 2008 and data collection started in July 2008. The study design, procedures and informed consent procedure were approved by the Medical Ethics Committee of the University Medical Center Groningen (No. 2007.217). All participants provided written informed consent. Guidelines were followed according to the Consort Statement [24].

### Study population

In the period April - June 2008, participants who were willing to start a "beginners 9-week program" in preparation for the Groningen 4-Mile running event were recruited with advertisements in local media in the northern part of the Netherlands. For this study participants were not obliged to participate in the Groningen 4-Mile running event. The Groningen 4-Mile running event is a popular annual recreational running event that takes place in October. After initial registration, potential participants were sent written information about the study along with a baseline questionnaire and invitation for an initial interview in the Center for Sports Medicine at the University Medical Center Groningen (UMCG), The Netherlands.

### Inclusion & exclusion criteria

Healthy subjects between 18 and 65 years of age who had no injury of lower extremities or lower back in the last three months prior to inclusion, who had not been running on a regular basis in the previous twelve months who were willing to start a beginners program were eligible for inclusion in the study. Potential participants were excluded to the study if there were absolute contraindications for vigorous physical activities according to the American College of Sports Medicine [25] or in case of unwillingness to keep a running log.

### Sample size

A power calculation was carried out for the main outcome variable, i.e. running related injury (RRI), using a logistic rank survival power analysis. As stated before, the incidence of RRIs varies between 19-79%.

A reduction of 25% on the incidence of RRIs in the PRECON group is considered clinically significant and relevant. The expected incidence of RRIs is 40% [4,10]. With a hypothesized 25% reduction of RRIs in the PRECON group compared to the control group, a total of 360 runners (2 × 180) is needed for a power of 80% and an alpha of 0.05. Assuming an attrition of 15% in the intervention period and follow up period, a total of 414 (2 × 207) novice runners are needed to detect an effect of the PRECON intervention.

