### Outcome measures

The primary outcome of the GRONORUN trial was the number of RRIs in both groups. A runner could only have one RRI. Definition of a RRI in this trial was; running related musculoskeletal ailment of the lower extremities or back, causing a restriction of running for at least one week, i.e. three consecutive training sessions.

Information on RRIs and exposure data was collected using an internet based running log. Each of the participants received a study number and a password to enter a personal environment of the web based training log. After each training week participants had to fill in their running activities, other sport activities and injuries.

Per training session the total minutes of running, total minutes of walking and injuries were registered. Data on injuries were collected by registering anatomical site of the body and severity of pain. Severity of pain was subdivided in pain without limitation (no RRI), pain that caused a restriction of running (scored as an RRI) and pain which made running impossible RRI (scored as an RRI). In case of skipping a training session, the reason (RRI, other injury, motivation, illness or remaining reason) for it was asked. When a "running related injury" was the reason for not training, information on anatomical site and severity was asked. To point out the anatomical site of an injury, a picture of the lower body was shown after reporting a RRI. By clicking on the anatomical site of the RRI, the same spot was appointed in red. When participants did not enter their digital training log after one week, a reminder was send by email automatically. In case of not having access to the Internet, all participants had also a hard copy of the running log.

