### Statistical analyses

To evaluate the success of the randomization, baseline characteristics of participants in the CON and PRECON group were compared using 2-tailed t-tests for normally distributed continuous variables. The χ^2 ^statistic was used for discrete variables. To evaluate the effect of the PRECON program on the number of injured runners in both groups, a χ^2^-test was used. The log-rank test is used to compare the Kaplan-Meier curves of the injured runners of the PRECON group and the CON group, analyzing the difference between these two groups in the probability of an RRI at any point in time. All analyses were performed following the "intention to treat" principle. Differences were considered statistically significant at P < .05. All analyses were performed using SPSS version 16.0 (SPSS Inc, Chicago, Ill).

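### The 360 runners (2 × 180) give about 51–52% power, not 80%, for 40% versus 30% injured; 80% power needs about 700–712 runners

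*Protocol article*

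**What the plan says.** In the Sample size section, the calculation is described as done "using a logistic rank survival power analysis". The expected injury incidence is 40%. The target effect is given as follows: "A reduction of 25% on the incidence of RRIs in the PRECON group is considered clinically significant and relevant". From these inputs the article concludes that "a total of 360 runners (2 × 180) is needed for a power of 80% and an alpha of 0.05". Allowing for 15% attrition, the total becomes 414 (2 × 207). Participant flow reports 432 randomised, 211 to preconditioning and 221 to control.

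The outcome is at most one event per runner: "A runner could only have one RRI". Statistical analyses plans a χ² test on the number of injured runners. It also plans a survival comparison: "The log-rank test is used to compare the Kaplan-Meier curves of the injured runners". The significance rule is "Differences were considered statistically significant at P < .05". The sample-size paragraph gives no sidedness, hazard ratio or event count.

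**The concern.** The paragraph contains every input needed to recompute the number, and the result does not follow from them. Detecting a fall from 40% to 30% with 180 per arm is well short of an 80% design under either planned test.

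This matters because the claimed 80% power is attached to the effect that the article itself calls clinically relevant. A reader who trusts it would take a non-significant result as fairly strong evidence against a 25% reduction. With power near 50%, such a result would be almost as likely as not even if preconditioning worked exactly as hoped. The Discussion expects the findings to be carried into training programs widely, so a misread null result would have consequences.

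**Working it through.** **Inputs.** Control incidence p₁ = 0.40, a 25% reduction so p₂ = 0.75 × 0.40 = 0.30, power 80% (z = 0.8416), alpha 0.05 and 1:1 allocation, all from Sample size except the allocation, which is from Randomization. Alpha is taken as two-sided (z = 1.96) in the base case, and one-sided is also tried.

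**Stated figure.** 180 per arm, 360 in total.

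**χ² test.** With mean proportion 0.35:

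n per arm = [1.96√(2 × 0.35 × 0.65) + 0.8416√(0.40 × 0.60 + 0.30 × 0.70)]² / (0.10)²
= (1.3221 + 0.5646)² / 0.01 = 355.9

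So 356 per arm, 712 in total (376 per arm, 752 in total, with continuity correction). The stated total is 360/712 = 51% of this.

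**Log-rank test.** Under proportional hazards, 40% versus 30% implies HR = ln 0.70 / ln 0.60 = 0.698, and ln 0.698 = −0.3592.

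- Schoenfeld: events = 4(1.96 + 0.8416)² / 0.3592² = 243. Divided by the mean incidence of 0.35, about 695 runners.
- Freedman: 249 events, about 710 runners.

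**Power with 2 × 180.**

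- χ²: Φ[(0.10√180 − 1.3221) / √0.45] = Φ[(1.3416 − 1.3221) / 0.6708] = Φ(0.029) = 51.2%. A simulation of 200,000 trials gave 51.7%.
- Log-rank: expected events 360 × 0.35 = 126, and Φ(√126 × 0.3592/2 − 1.96) = Φ(0.056) = 52.2%.

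**Power with the numbers randomised.**

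| Runners | χ² | Log-rank |
|---|---|---|
| 360 | 51.2% | 52.2% |
| 367 (432 × 0.85) | 51.9% | 53.0% |
| 432, no loss | 58.7% | 59.8% |

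**Detectable effect with 360.** Solving the same formulas for 80% power gives p₂ = 26.2% (χ²) or 26.4% (log-rank), a relative reduction of 34–35%.

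**Other readings of the inputs (runners per arm for 80% power; the plan has 180).**

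| Reading | Per arm |
|---|---|
| 40% v 30%, one-sided | 274–280 |
| 25 percentage points (40% v 15%), two-sided | 49 |
| 25% lower hazard (HR 0.75), two-sided log-rank | 528 |
| 40% as the preconditioning rate (53.3% v 40%), two-sided | 219 |
| Same, one-sided | 173 (187 with continuity correction) |
| 40% as the injury-free proportion (60% v 45% injured), two-sided | 173 (186 with continuity correction); log-rank 164–169 |

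None gives 180. The last two rows come near it but contradict the text, which gives 40% as the expected incidence of injury and measures the reduction against the control group. With one-sided alpha and 40% versus 30%, power at 360 is about 64%. With a 25% relative reduction, 180 per arm fits only a control incidence of about 58–59%.

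**The case against.** The strongest counter-argument is that the power statement is conditional on a planning guess. At higher incidence the same 2 × 180 would suffice: for a 25% relative reduction, χ² power is about 67% at 50% incidence, 82% at 60% and 98% at 79%. That is true, but at 19%, the low end of the article's quoted range, power is about 23%. That range comes from different populations, and the article chose 40%. The sentence is wrong for the value it adopts.

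Second, the cause is not known. The required per-arm number (356) is close to the stated total (360), so a per-arm figure may have been entered as the total. Confusing injured with injury-free runners (60% v 45%) is a competing explanation. Neither is documented, and the error does not depend on which is right.

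Third, counting 432 less 15% as 367 treats each dropout as contributing nothing. In a log-rank analysis, runners lost part-way contribute time and events up to loss, so the power lies between the 367 and 432 figures, about 53–60%. This stands, and the corrected text should give a range.

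Fourth, the odd name for the method is a wording matter. Read with the Statistical analyses section it evidently means the log-rank test, and it does not affect the numbers. Nor does the article itself say that a non-significant result will be read as no effect; that is a risk created by the 80% claim.

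**Conclusion.** The concern holds. For the stated 40% incidence and 25% relative reduction, at two-sided alpha 0.05, 360 runners give 51–52% power, and 80% power needs about 695–712. The χ² and log-rank calculations agree. The conclusion does not rest on sidedness, since one-sided power is about 64%, or on attrition, since all 432 with complete data would reach only 59–60%. It assumes that the reduction is relative, as the wording indicates, and, for the log-rank figures, proportional hazards. This is an explicit statement with complete inputs and a wrong result, so it is not a detail left to a fuller protocol or analysis plan. It must be corrected because it is the central design claim and is out by a factor of about two.

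**What to change.** Correct the sample-size paragraph to say:

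- For 40% versus 30% injured, two-sided alpha 0.05 and 80% power, about 700–712 evaluable runners (about 245 injured runners) are needed.
- The 432 randomised give about 52–53% power if 15% are lost and contribute nothing, rising to 59–60% with no loss.
- After 15% attrition, 80% power exists only for a relative reduction of about 34%.
- The calculation is for the log-rank test, with its sidedness stated.

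Alongside this, report the effect estimate with its 95% confidence interval and say that a non-significant result will not be read as absence of effect. That addition is good practice given the true power, but it is separate from the arithmetic.

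Recruitment is complete and no extra runners are proposed. The cost is a reworded paragraph and a less favourable stated power.

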### Participant flow

The study design and participants flow are shown in Figure 1. A total of 500 people were interested to participate in the GRONORUN 2 study and responded to the call for novice runners. To all of those who reacted on the advertisements, an information brochure in which the study protocol was clearly described, a baseline questionnaire and an appointment at the UMCG was given. Forty four did not confirm their appointment for the initial interview nor filled in the baseline questionnaire. Of those who confirmed the appointment for the initial interview and filled in the questionnaire (n = 456), four failed to attend the initial interview. Eventually, of the 452 persons who visited the UMCG for an initial interview, 20 were excluded. Reasons for exclusion were: already participating in running (n = 11), musculoskeletal injury of lower extremities or back at baseline (n = 6) and contraindications for vigorous physical activity (n = 3). After baseline measurements and stratification, 432 participants were randomly assigned to the intervention group (n = 211) and to the control group (n = 221).

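### The 15% attrition allowance multiplies 360 by 1.15 to give 414; dividing by 0.85 gives 424, a slip worth about one point of power that the 432 randomised already cover

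*Protocol article*

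**What the plan says.** The Sample size section of the protocol article gives the requirement before losses: "a total of 360 runners (2 × 180) is needed for a power of 80% and an alpha of 0.05". The next sentence makes the allowance for losses and gives the enrolment target: "Assuming an attrition of 15% in the intervention period and follow up period, a total of 414 (2 × 207) novice runners are needed". No inflation formula is printed.

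The Participant flow section reports the number enrolled: "432 participants were randomly assigned to the intervention group (n = 211) and to the control group (n = 221".

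The Statistical analyses section plans a χ² test on the number of injured runners and a log-rank test on the Kaplan-Meier curves, both by intention to treat.

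**The concern.** An attrition allowance should make the number left after the expected losses equal the number required. The target of 414 looks like the requirement plus 15% of itself, which does not do that. Because 15% of a larger number is lost, more is taken away than was added.

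Readers use the printed target to judge whether the trial met its own plan. A target that falls short of its own requirement is an error in the text even when the gap is small. The same operation would also carry over to any revised base figure, where the gap in runners grows in proportion.

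**Working it through.** **Inputs** (protocol article)

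- Required before losses: 360 in total, 180 per arm (Sample size).
- Attrition: 15%, occurring during the intervention and follow-up periods (Sample size).
- Stated target: 414 in total, 207 per arm (Sample size).
- Power 80%, alpha 0.05 (Sample size). Sidedness is not stated; two-sided is assumed below.
- Randomised: 432, as 211 and 221 (Participant flow).

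**Step 1. Reproduce the stated figure.** n × (1 + d):

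- 360 × 1.15 = 414
- 180 × 1.15 = 207

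Both match exactly, so rounding does not explain the figure.

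**Step 2. Test it against the requirement.** Number left = N × (1 − d):

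- 414 × 0.85 = 351.9, about 352 (207 × 0.85 = 175.95, about 176 per arm)
- Shortfall: 360 − 352 = 8 runners
- Largest attrition at which 414 still leaves 360: 1 − 360/414 = 13.0%

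**Step 3. Apply the allowance to those enrolled.** n / (1 − d):

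- 360 / 0.85 = 423.5, rounded up to 424
- 180 / 0.85 = 211.8, rounded up to 212 per arm
- Difference from the stated target: 424 − 414 = 10 runners, or 10/414 = 2.4%

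**Step 4. Effect on power, taking as given that 360 provides 80%.** With the effect held fixed, the expected test statistic scales with √n, so

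power ≈ Φ[(1.960 + 0.842) × √(n/360) − 1.960].

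- n = 351.9: √(351.9/360) = 0.9887; 2.802 × 0.9887 − 1.960 = 0.810; power ≈ 79.1%
- n = 367.2: √(367.2/360) = 1.0100; 2.802 × 1.0100 − 1.960 = 0.870; power ≈ 80.8%

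**Step 5. The number actually randomised.**

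- 432 × 0.85 = 367.2, about 367 left at 15% attrition, above 360
- Largest attrition at which 432 still leaves 360: 1 − 360/432 = 16.7%

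**The case against.** The best defence is that nothing follows from the slip. The number randomised exceeds both 414 and 424, recruitment closed in June 2008, and no choice of design or analysis depends on the difference. All of this stands, and it is why the point carries the lowest severity. It does not make 414 the right result of the stated inputs.

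A second defence is that counting 352 treats every drop-out as contributing nothing. The power calculation is described as a survival one, and a log-rank test is planned. A runner lost part-way contributes follow-up time, and possibly an injury, before being censored. This also stands: for the log-rank test, 8 is an upper bound on the effective loss. The χ² comparison of the number injured has less of this protection, so the objection narrows the point without removing it.

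A third defence would read the 15% as a fraction of those who complete: 54/360 = 15%, whereas 54/414 = 13.0%. The text does not support this reading. It places the attrition in the intervention and follow-up periods, which makes it a loss from those enrolled, and it gives no other definition.

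In the other direction, a reader might infer an arm-level shortfall, because 211 is below 212. That is not a meaningful deficit. At 15% attrition the arms keep 211 × 0.85 = 179.35 and 221 × 0.85 = 187.85. Two arms of those sizes carry the information of 4 × 179.35 × 187.85 / 367.2 = 367.0 runners split equally, still above 360. Drawing envelopes within eighteen strata also need not end in equal arms.

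**Conclusion.** Wrong as written, at the lowest severity. The base, the attrition rate and the target are all printed, and the three do not agree: 414 should be 424. The size is 10 runners in the target, at most 8 runners after losses, and about one point of power (80% to about 79%).

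The target correction rests only on reading attrition as a loss from those enrolled. The power figures also take the plan's premise that 360 gives 80%, assume a two-sided test, and count drop-outs as contributing nothing.

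A reader might infer that this slip leaves the trial seriously short of power. The documents do not support that. On the plan's own premise, the 432 randomised leave about 367 and slightly more than 80% power. Whether 360 follows from the stated 40% incidence and 25% reduction is a separate question. The attrition step is no evidence on it, and correcting that step would not settle it.

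**What to change.** In the Sample size section, replace 414 (2 × 207) by 424 (2 × 212). Add a sentence saying that the 432 participants randomised exceed this target and leave about 367 at 15% attrition. If the base of 360 is revised for any other reason, divide the revised figure by 0.85 and use that result in place of 424.

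The cost is one corrected number and one sentence. No further enrolment is needed, and the design and analysis do not change.
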